### Omics data and analyses

#### Microbiome data processing and analyses

PCR of 16S rRNA gene amplicons will be sequenced by an Illumina Miseq high-throughput platform and pair-end modality using standard protocols. Selected samples will be subjected to shotgun metagenomic library construction using the TruSeq DNA PCR-Free Library Preparation Kit by Illumina. The resulting 16S rRNA gene amplicon sequences will be analysed using the QIIME 2 microbiome bioinformatics platform [156]

For oral and intestinal microbiome data, we will perform principal coordinates analysis to investigate the compositional differences between samples. The cases and control groups will be compared concerning microbial diversity (alpha- and beta-diversity) and taxonomic abundances. Here methods developed for microbiome data to account for sparsity and under-sampling of the microbial community will be applied, such as implemented in the R package (phyloseq) [157, 158]. Correlations between microbial species will be mapped using sparCC [159], which is designed for compositional data such as microbial relative abundances and compared between case and control groups to reveal potential differences in the microbiome community structure. Shotgun metagenomic reads will be quality filtered to remove low-quality regions and screened for human reads. The taxonomic annotation will be performed using QIIME 2 [160]. Reads will be mapped against the human gut microbial integrated gene catalogue (IGC) [161]

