Loss of intestinal barrier function may lead to subsequent increased serum levels of microbiota-derived molecules and, in turn, activation of the immune system, which may lead to neuroinflammation. This has been described in several neuroimmune disorders such as ASD [1, 4, 7], chronic fatigue syndrome [8], major depressive disorders (MDDs) [9, 10], and schizophrenia [11, 12].

It is vital to study the intestinal microbiota and IP further regarding diet and mental health [56]. It is important to overcome previous limitations and increase the number of subjects, coordinate strategies, and assess confounding factors, e.g., the severity of the mental disorders and problems from the GI tract, and secure quality collection [94, 122] as well as lifelong medication use. Biosamples will be collected and analyzed with the latest technology factors in addition to the microbiota, that can shed a better light on research questions and potential mechanisms. As data on the gut-brain axis demonstrates association between intestinal microbiota composition and mental disorders such as depression, we will collect fecal samples within this study for microbiome analysis. However, longitudinal studies are lacking, and therefore in this present study, collection of data will be repeated in three years. These are the basis of the current study on Meals, Microbiota and Mental Health in Children and Adolescents, i.e., the MMM study.

Our hypothesis for the current study is the following; There are differences between cases and controls regarding dietary intake, nutritional status and/or the intestinal microbiota and related metabolic factors, in physical symptoms from the digestive tract and in intestinal permeability. In addition, we hypothesize that there are differences in other potentially relevant background factors and therefore comparisons with full siblings will give insight into family variability.

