#### Sample size

Power calculations were performed for detecting mean difference (independent sample t-test) intestinal permeability using unmatched case-control with an ⍺ of 0.05 and β of 20% (i.e., power of 80%) with 1:1 ratio of cases vs. controls [123, 124]. The prevalence of IP among cases was calculated at 30%. However, assuming 10% prevalence in controls, the minimum number of children in each arm of the study is 62. However, as our case group covers a relatively broad spectrum of mental disorders (often overlapping individually) that will be examined in smaller case groups, the aim is set at a minimum of 100 participants in each arm (70% participation rate). The current study is an observational and non-intervention study, and therefore it is not possible to calculate power for all the factors that will be compared between the cases and controls. Corrections will be made for multiple comparisons.

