### Sample collection

All biosamples, except blood, will be collected at home by the participants, with help from their guardians when needed. A biosample kit will be delivered to the participants and collected by research staff to make sure the samples will be in good condition and usable. Participants are asked to collect the biosamples preferably towards the end of the 3-day food registration within the first month into the study and store the biosamples in a specific container in a cool dry place (4–8°C) according to the manufacture’s guidelines. Commercial kits from DNA Genotek´s microbiome stool collection kits are used to collect and optimally stabilize stool samples. Fecal and saliva samples will be collected for microbiome 16s rRNA amplicon sequencing. A buccal swab will be collected for whole-genome genotyping of human DNA. Urine samples will be collected for targeted analysis of food-related peptides and untargeted metabolomics profiling. Blood will be collected either at Landspitali, University Hospital in Reykjavik, or Akureyri Hospital in Akureyri, depending on residence, for analyzing serum zonulin, inflammatory biomarkers, e.g., CRP, interleukins, and nutritional status, i.e., hemoglobin, ferritin, folic acid, Vitamin B_12_, 25-hydroxy-vitamin-D, and fatty acids. The biosamples are preferable to be collected towards the end of the 3-day food registration according to standard procedure as mentioned above. The kit is then collected from both cases and controls by the researchers along with the food diary in Reykjavik, Akureyri, and near surroundings. Participants will be able to deliver the samples to a provided location if they prefer. For other locations in Iceland, the samples will be sent out, including guidelines on how to resend them to the researchers after their collection. The urine samples will be aliquoted into smaller tubes for storing at a laboratory unit at the University Hospital or Akureyri Hospital in a -80°C freezer along with the other biological samples.

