#### Integrative analysis of Meals, Microbiota, and Mental Health data

For each type of omics- and biomarker data (nutrients, microbiota, metabolomics, food-related peptides, inflammatory factors), appropriate preprocessing, and quality control will be coordinated and performed by the researchers. All data will be appropriately normalized and transformed, checked for potential batch effects and outliers removed. The effects of potential confounders such as age, sex, body mass index, ROME IV (for intestinal microbiota), medication, or diet will be investigated. For each datatype cases will be compared to the two control groups, but also associations between the different variables will be looked for separately, as well as in relation to sub-groups, using multivariate models including adjustments for confounder variables. Using analysis of covariance (ANCOVA) the influence of potential confounders such as age, sex, body mass index, ROME IV (for intestinal microbiota), medication and diet will be investigated. Benjamin-Hochberg false discovery rate will be applied, correcting for multiple hypothesis testing.

Integrating different types of high-dimensional omics data is a challenging task, and multiple approaches can be undertaken. A computational framework for such analysis [163] has been suggested based on dimensionality reduction of omics data using co-abundance clustering, followed by cross-omics correlation analysis focused on features that differ between cases and controls. In addition, other types of omics integration approaches will be applied, as recently reviewed [164, 165], such as robust sparse canonical correlation, co-inertia, or Procrustes analysis, to identify shared patterns across omics and dietary data in the context of mental health.

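### The SparCC network comparison takes no covariates, so the planned medication adjustment cannot reach it; repeat it in cases without current psychotropic use

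*Protocol article*

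**What the plan says.** Under Microbiome data processing and analyses, the protocol article maps correlations between microbial species with SparCC. These are to be "compared between case and control groups to reveal potential differences in the microbiome community structure". No stratum, restriction or handling of medication is stated for this step.

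Under Integrative analysis of Meals, Microbiota, and Mental Health data, the article deals with confounding by covariate models (multivariate models and ANCOVA): "The effects of potential confounders such as age, sex, body mass index, ROME IV (for intestinal microbiota), medication, or diet will be investigated". The Introduction, in the section on diet, intestinal microbiota and mental disorders, also names medication history among the things to be handled: "secure quality collection [94, 122] as well as lifelong medication use".

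Table 1 admits cases at first referral to the clinic. The only drug exclusion in any group is antibiotics within four weeks. Both control groups exclude children with a mental disorder diagnosis. Under Data collection, medication is recorded by questionnaire and, if guardians allow, by registry dispensing data from birth. The abstract calls national psychotropic use very high but gives no rate, for cases or for controls.

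**The concern.** Read together, the eligibility rules make psychotropic exposure close to a subset of case status. That follows from who may enter each group; it is not a figure in the article. The stated protection against this confounder is a covariate in a regression-type model. SparCC estimates correlations among taxa within a group and has no place for a covariate, so the protection does not extend to the one analysis that the article names for community structure.

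What is at stake is the interpretation of any network difference. If some cases take a drug that moves several taxa together, those taxa will be correlated among cases and not among controls, even when the disorder itself has no effect on them. The network comparison alone could not separate the two explanations.

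**Working it through.** **Inputs.** From the article: 100 children per group (Sample size: "the aim is set at a minimum of 100 participants in each arm (70% participation rate"). Assumed, because the article gives none: the share m of cases on psychotropics, the size of the drug effect, and the share q of each group on other medicines. No disorder effect is assumed throughout.

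**The article's own figure.** It gives none for this point. Its sample size reproduces: for 30% against 10%, two-sided 5% and 80% power, n = [1.96·√(2·0.2·0.8) + 0.8416·√(0.3·0.7 + 0.1·0.9)]² / 0.2² = (1.109 + 0.461)² / 0.04 = 61.6, so 62 per arm as stated. The present point uses only the target of 100.

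**1. Network comparison.** Let a drug shift two otherwise independent taxa, on a standardised scale, by s in a fraction m of cases and in no control. The correlation induced in cases is r = m(1−m)s² / [1 + m(1−m)s²]; in controls it is 0.

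- m = 0.5, s = 1: r = 0.25/1.25 = 0.20.
- Fisher z: atanh(0.20) / √(2/97) = 0.203/0.144 = 1.41. The chance of flagging a difference at two-sided 5% is 29%.
- m = 0.3 or 0.7, s = 1: r = 0.21/1.21 = 0.174; chance 23%.
- s = 0.5: r is 0.05 to 0.06; chance 6% to 7%, little above the nominal 5%.

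These are chances per pair of taxa, before any correction for multiplicity. Among untreated cases the induced correlation is 0 under this model, so restriction removes it.

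**2. Covariate models, if the medication term pooled all drugs.** Take m = 0.5, a drug effect of 0.5 SD, and q = 0.2 in each group, independent of psychotropic use. Other medicines have no effect.

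- Unadjusted shift: 0.5 × 0.5 = 0.25 SD.
- Share on any drug: cases 1 − 0.5·0.8 = 0.6; controls 0.2.
- Within-case covariance of the any-drug indicator with the outcome: 0.5 × (0.5 × 0.4) = 0.10. Within-group variances of the indicator: 0.24 and 0.16.
- Coefficient of the pooled term: 0.10/0.40 = 0.25.
- Left in the case coefficient: 0.25 − 0.25 × (0.6 − 0.2) = 0.15 SD.

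The same algebra over m = 0.3 to 0.7 and q = 0.1 to 0.3 gives 0.07 to 0.25 SD. At m = 0.5 and q = 0.3 it gives 0.18 SD; simulation (4,000 runs) agrees, with about 23% rejections at the 5% level.

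**3. Covariate models with a psychotropic-specific term.** If no control takes psychotropics, the case coefficient is the contrast of untreated cases with controls. Simulation gives a mean of about 0 and rejection of 4% to 5%, even when two drug classes with different effects share the term. The price is precision: variance rises by the factor [1/(1−m) + 1]/2.

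| m | variance factor | detectable difference, 80% power (SD) |
|---|---|---|
| 0 | 1.00 | 0.40 |
| 0.3 | 1.21 | 0.44 |
| 0.5 | 1.50 | 0.49 |
| 0.7 | 2.17 | 0.58 |
| 0.9 | 5.50 | 0.93 |

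**The case against.** The strongest reply is that medication is already planned for. The article lists it as a confounder, collects it from two sources, and says that each data type will be compared using adjusted models. That stands for the diversity and abundance comparisons, which fall under those models. It does not reach SparCC. SparCC networks can be compared within strata or restricted groups, but the article states no such step.

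Several stronger readings are tempting and are not supported:

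- A reader might infer that the models use one yes/no term for all medicines. The article gives an open list of confounders and no coding, and a condensed article commonly leaves coding to the full protocol or analysis plan. The 0.15 SD figure is therefore conditional: it shows why drugs should not be pooled, not that they will be.
- A reader might quote the error rates of unadjusted comparisons (18%, 42% and 70% with 30%, 50% and 70% of cases treated and a 0.5 SD effect). Adjusted models are planned, so these do not describe the main comparisons.
- The principal coordinates analysis also takes no covariates, but it is a descriptive ordination with no test stated.
- A reader might infer that children start treatment while samples are being taken, since collection is "preferably towards the end of the 3-day food registration within the first month into the study". Nothing in the article says so, and its introduction notes that guidelines usually do not favour medication first except in severe cases. Some first-visit cases may well be untreated.
- It would be too strong to say that drug effects will be reported as effects of the disorder. Table 3 limits conclusions to association. That limit does not, however, tell the reader whether an association goes with the disorder or with its treatment.

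**Conclusion.** The point holds in a narrow form. One named analysis, the SparCC comparison, leaves open a confounder that the article itself names, because the stated adjustment is of a kind that SparCC cannot use.

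The size is unknown, since the article gives no rate of psychotropic use and no drug effect. On assumed inputs it runs from almost nothing (6% to 7% flagged per pair for a 0.5 SD shift) to material (23% to 29% for a 1 SD shift with 30% to 70% of cases treated). These figures rest on no psychotropic use in controls, a simple shift in two taxa, and a Fisher z comparison standing in for the network test. For the covariate models there is no demonstrated error, only a reason to keep psychotropics apart from other medicines. This is a cheap improvement, not a flaw that undermines the study.

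**What to change.** In Microbiome data processing and analyses, add that the SparCC comparison will be repeated, and the principal coordinates plot shown, for cases without current psychotropic use against each control group. Define current use from the medication questionnaire and, where guardians allow, from the registry data. Report this as a sensitivity analysis, with symptom severity scores for treated and untreated cases beside it.

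In the integrative analysis section, state that current psychotropic use enters the models separately from other medicines. If the full protocol or analysis plan already does either, a cross-reference is enough.

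The cost is a few lines of text and one repeat of the network comparison, with no new data and no change to any child's treatment. The restricted contrast has fewer cases and wider intervals. With half of the cases treated, the standard error of a Fisher z difference rises from √(2/97) = 0.144 to √(1/47 + 1/97) = 0.178, or by 24%. Untreated cases may also be milder, so a difference that disappears on restriction could reflect severity or lost precision as well as treatment. In the covariate models the cost is the loss of precision shown in the table above.

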#### Urine metabolomics processing and analyses

A morning urine sample is collected at home in a tube with peptide inhibitors. The urine is divided into two samples, one for targeted analysis of food-related peptides on an HPLC reverse phase (C-18) chromatography that gives the total peptide amount related to creatinine. The other urine sample will be used for untargeted metabolomics profiling (LC-ESI-qTOF-MS). All raw data will be extracted and processed using Agilent MassHunter Qualitative Analysis B.07.00 software. A list of peak areas, retention time and mass to charge (m/z) will be obtained and metabolites will be identified by comparing the data to selected databases. Multivariate statistical analysis will be performed using MetaboAnalyst 3.0 [162].

#### Serum measurements analyses

Concentrations of serum zonulin will be determined by ELISA assays according to the manufacturers’ protocols from Immundiagnostik AG (Bensheim, Germany) but performed at the Mucosal Immunology and Biology Research Center at the Massachusetts General Hospital in Boston. Inflammatory biomarkers will be determined by multiplex immunoassays based on the mesoscale discovery platform (e.g., CRP, interleukins) and nutritional status (hemoglobin, ferritin, folic acid, 25-hydroxy-vitamin-D, ⍵-3 fatty acids) by kits in the Landspitali laboratory in Reykjavik.

#### Nutritional analyses

For the nutritional data, the FFQs will be analyzed through PCA identifying dietary patterns in the groups. At the same time, the three-day registration will be reviewed by a dietitian and used to calculate a more exact intake of food items, calculated forward into nutrients (energy, macronutrients (protein, fat, carbohydrates/fibers)) and micronutrients (vitamins, minerals, and other bioactive compounds). Data with mean energy intake below the Basal Metabolic Rate (BER) of the child will be excluded. Furthermore, the dietary data, as well as information on the nutritional status, inflammatory factors, and omics data, will be used to study associations with oral and fecal microbiota. The same analysis will also be made in the more significant subgroups, for example, children with ADHD or ASD.

#### Genetic data and analyses

Whole genome genotyping will be performed on human DNA isolated from buccal swab samples. Genotype data on study participants will be used to investigate how host gene anchors might predict or interact with particular microbiota. Here the focus will be on genetic variants previously associated with microbiota composition or psychiatric disorders.

#### Integrative analysis of Meals, Microbiota, and Mental Health data

For each type of omics- and biomarker data (nutrients, microbiota, metabolomics, food-related peptides, inflammatory factors), appropriate preprocessing, and quality control will be coordinated and performed by the researchers. All data will be appropriately normalized and transformed, checked for potential batch effects and outliers removed. The effects of potential confounders such as age, sex, body mass index, ROME IV (for intestinal microbiota), medication, or diet will be investigated. For each datatype cases will be compared to the two control groups, but also associations between the different variables will be looked for separately, as well as in relation to sub-groups, using multivariate models including adjustments for confounder variables. Using analysis of covariance (ANCOVA) the influence of potential confounders such as age, sex, body mass index, ROME IV (for intestinal microbiota), medication and diet will be investigated. Benjamin-Hochberg false discovery rate will be applied, correcting for multiple hypothesis testing.

Integrating different types of high-dimensional omics data is a challenging task, and multiple approaches can be undertaken. A computational framework for such analysis [163] has been suggested based on dimensionality reduction of omics data using co-abundance clustering, followed by cross-omics correlation analysis focused on features that differ between cases and controls. In addition, other types of omics integration approaches will be applied, as recently reviewed [164, 165], such as robust sparse canonical correlation, co-inertia, or Procrustes analysis, to identify shared patterns across omics and dietary data in the context of mental health.

## Discussion

Investigating the interaction between diet, intestinal microbiota, IP, and their associations with mental health and comparison to healthy controls is an original and novel study. The Child and Adolescent Psychiatry Department (BUGL) at Landspitali, the National University Hospital of Iceland is the *only* psychiatric department for children and adolescents. This is the first population-based study enrolling all children with the most severe mental disorders assessed both categorically and dimensionally for one year and matched controls. This approach will provide valuable information on the relationship between these three domains offering crosstalk between different disciplines, to identify novel associations and potential mechanisms involved in neurodevelopmental disorders. There is a call for more population-based multidimensional transdisciplinary studies designed for improving mental health and our study fits well with priorities recently put forward in the Roadmap for Mental Health Research in Europe [166]. Furthermore, the World Health Organization (WHO) has recently called for a stronger focus on adolescent’s health, with depression as the number one cause of illness and disability in this age group [167]. Along with increasing the amount and precision of clinical information collected, the longitudinal approach of the MMM study will improve both reliability and validity of psychiatric diagnoses in line with LEAD (Longitudinal, Expert, All Data) procedure [168]. Furthermore, collection of multi-omics data and clinical correlates otherwise missing in this unique study population is of importance. Repeating data collection in the same groups in three years, when majority of children will be in their adolescence, gives a valuable opportunity to observe changes especially as studies on mental health are lacking in this age group [169, 170]. More multidimensional transdisciplinary studies including longitudinal observational data have been called for as a basis for lifestyle treatment options for improving mental health and wellness [169, 170]. Importantly, the longitudinal design also allows for determining if the baseline dietary, microbiome, and metabolome patterns are predictive of future outcomes, which may aid the definition of biomarker-based diagnostic tools and therapeutic interventions. The novelty of this longitudinal observational case-control study in children and adolescents resides in the new way of approaching mental disorders holistically. Using longitudinal experts diagnoses with simultaneous use of categorical and dimensional assessments using recognized and validated rating scales, identifying patterns between the leading players of meals, intestinal microbiota, IP, and mental health has never been done before. The strengths and limitations of this study are outlined in Table 3.

**Table 3 pone.0273855.t003:** Strengths and limitations of the MMM study.

⇒ This is the first observational study evaluating diet, microbiota, intestinal permeability, and mental health in children and adolescents in Iceland. ⇒ Recognition of the relationship between the gut-brain axis and the neuro-immune system provides a novel approach for better understanding and managing mental disorders. ⇒ More multidimensional transdisciplinary studies including longitudinal observational data have been called for as a basis for lifestyle treatment options for improving mental health and wellness. ⇒ The study will use two control groups, i.e., full siblings living in the same household close in age and age and sex-matched children from the same postal area, which is another strength of the study. ⇒ Limitations are mainly the willingness to participate as full participation, although priceless for science, is demanding. ⇒ This study will highlight associations but not causation. ⇒ Multiple variables being assessed which makes it more challenging to get at mechanisms. ⇒ Mental health molecular changes may occur years before symptoms making it difficult to determine linear relationship. ⇒ The longitudinal follow-up will help but as diet and microbiome sampling will be done 3 years out it will be even more difficult to fully state if any of the variables had an influence on mental health.

The project is a cooperation between the Unit for Nutrition Research, Faculty of Food Science and Nutrition, University of Iceland and BUGL, as well as the Department of Infectious Diseases, both at Landspítali University Hospital, but includes also national and international partners. Domestic co-operation between institutions is vital in this type of inter-disciplinary research, and all participating researchers are well-established experts in their fields. Consequently, these researchers possess complementary expertise necessary to complete the research project and answer the scientific questions put forward.

The data will give multiple possibilities for further scientific writings, as well as longitudinal data after three years. Information on publications from the study will be published on the MMM web page www.mmmrannsoknin.hi.is and on social networking sites for scientists and researchers, i.e., Akademia.edu (USA) and ResearchGate.net (Europe) and social media such as Twitter and LinkedIn. This extensive dataset will be able to answer many scientific questions and will be open to other researchers after the study period.

